### Sample size calculations

As a trial embedded within a larger study, sample size calculations were not performed to power this trial. The main IPSAZ study has a target sample size of 1000 pregnant women, based on an estimated composite STI prevalence of 30%, a desired precision of 3%, an alpha of 0.05, and an additional 10% of participants to account for invalid test results
^
6,
25–
33
^.

From the initial pilot data from the IPSAZ study, we estimated a 30% prevalence of curable STIs and a recruitment rate of 5 participants per clinic day. For analysis, each clinic day will be considered as a unit of randomisation. It is therefore predicted that 300 index participants will receive partner notification slips, over 200 recruiting clinic days. This equates to 100 ‘clusters’ per arm, with an average of 1.5 participants per cluster.

The intra-cluster correlation coefficient (ICC) is assumed to be zero as the outcome is not expected to be more or less likely in participants having attended on the same day, compared to on different days. However, given the very small size of the clusters, even if the ICC was higher, it is unlikely to have a meaningful effect on the design effect size.

Initial data suggest that an estimated 30% of indexes have at least one partner returning for treatment. Assuming this, and an alpha of 0.05, a power of 0.8, an ICC of zero, 100 clusters per arm, and 1.5 participants per cluster, results in a minimum detectable odds ratio of 1.96 for the intervention (
Table 1). A higher ICC of 0.10 results in a minimum detectable odds ratio of 1.99.

**Table 1. T1:** Minimum detectable odds ratios for effect size of intervention, for differing proportions meeting the primary outcome in the control arm, assuming an alpha of 0.05, 100 clusters per arm, and 1.5 participants per cluster.

		ICC = 0.0		ICC = 0.1	
Sample size	Proportion meeting primary outcome in control arm	Smallest odds ratio detected at 80% power	Smallest odds ratio detected at 90% power	Smallest odds ratio detected at 80% power	Smallest odds ratio detected at 90% power
300	20%	2.09	2.33	2.13	2.37
	25%	2.01	2.22	2.04	2.27
	30%	1.96	2.17	1.99	2.21
	35%	1.93	2.13	1.96	2.17
	40%	1.92	2.12	1.95	2.16

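### The stated detectable odds ratios (1.96 and 1.99) are modestly optimistic: 300 indexes ignores the 10% invalid-test allowance, and the ICC 0.1 columns assume equal clusters of 1.5

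*Protocol article*

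**What the plan says.** All of this stands in the protocol article under Sample size calculations.

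- The parent study plans for 1000 women, a number derived from a 30% prevalence to be estimated within 3 percentage points. It also includes a margin, described as "an additional 10% of participants to account for invalid test results".
- The inputs for this trial, from pilot data: "we estimated a 30% prevalence of curable STIs and a recruitment rate of 5 participants per clinic day".
- The projection: "It is therefore predicted that 300 index participants will receive partner notification slips, over 200 recruiting clinic days". The section then restates this as 100 randomised units in each arm, "with an average of 1.5 participants per cluster".
- The result, for 30% of control indexes having a partner return: a minimum detectable odds ratio of 1.96 at 80% power and ICC 0. For the sensitivity case, "A higher ICC of 0.10 results in a minimum detectable odds ratio of 1.99".

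Table 1 gives 20 such odds ratios, all for a sample size of 300. The section also says that no calculation was done to power this trial.

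Elsewhere, Outcomes lists slip uptake as a secondary outcome, Ethics and dissemination leaves the decision to notify with the woman, and Statistical analysis uses women given a slip as the denominator.

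**The concern.** Two inputs do not sit with the section's own figures. First, the number of indexes is taken from all 1000 women, although part of the 1000 was added because some tests will be invalid. Full slip uptake is assumed as well. Second, an average of 1.5 per day is treated as if every day supplied 1.5 indexes. With so few women per day, many days will have no index and others will have two or more. The design effect depends on that spread.

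Both inputs make the detectable effect look smaller than it is. Because no sample size was set for this trial, Table 1 is the article's only quantitative statement of what the trial can detect. The Discussion's judgement that the trial is likely to have moderate power has no other numerical support there.

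**Working it through.** **Inputs (Sample size calculations).** 1000 women; 10% invalid-test allowance; 30% prevalence; 5 women per day; 200 days; control rate 30%; alpha 0.05 (taken as two-sided, which reproduces the table).

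**1. Reproduce the plan's figures.** The pooled two-proportion formula, without continuity correction, with n per arm, p1 = 0.30 and p2 = p1·OR / (1 − p1 + p1·OR):

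power = Φ{ [ (p2 − p1) − 1.96·√(2p̄(1 − p̄)/n) ] / √( [p1(1 − p1) + p2(1 − p2)]/n ) }

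At n = 150 and OR = 1.96: p2 = 0.588/1.288 = 0.4565, p̄ = 0.378, and power = Φ{(0.1565 − 0.1098)/0.0553} = 80%. Solving for exactly 80% gives OR 1.958. For ICC 0.1, dividing n by 1 + (1.5 − 1) × 0.1 = 1.05 gives 1.990. All 20 cells of Table 1 agree to within about 0.01.

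**2. Is the 10% inside the 1000?** 1.96² × 0.3 × 0.7 / 0.03² = 896. Then 896 × 1.1 = 986, or 896 / 0.9 = 996. So the 1000 already contains the allowance.

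**3. Indexes if the whole allowance is used up.** 1000 × 0.9 × 0.30 = 270 (or 1000/1.1 × 0.30 = 273).

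**4. Cluster sizes implied by the stated rates.** Assume 5 women every day and independent positivity, so the daily number of indexes m is Binomial(5, q). The design effect for variable size is 1 + (E[m²]/E[m] − 1) × ICC.

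| | q = 0.30 (300 indexes) | q = 0.27 (270 indexes) |
|---|---|---|
| Days with no index | 0.7⁵ = 16.8% | 0.73⁵ = 20.7% |
| Contributing days per arm | 83 | 79 |
| Mean size of these | 150/83.2 = 1.80 | 135/79.3 = 1.70 |
| E[m²]/E[m] | 3.30/1.50 = 2.20 | 2.808/1.35 = 2.08 |
| Design effect, ICC 0.1 | 1.12 | 1.108 |

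**5. Minimum detectable odds ratio, control 30%.**

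| Indexes | ICC | Design effect | 80% power | 90% power |
|---|---|---|---|---|
| 300 (Table 1) | 0 | 1 | 1.96 | 2.17 |
| 270 | 0 | 1 | 2.03 | 2.26 |
| 300 (Table 1) | 0.1 | 1.05 | 1.99 | 2.21 |
| 300 | 0.1 | 1.12 | 2.03 | 2.26 |
| 270 | 0.1 | 1.108 | 2.10 | 2.35 |

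At ICC 0, power at OR 1.96 is 80% with 300 indexes and 76% with 270. The detectable rates at ICC 0 are 45.6% (OR 1.958) and 46.5% (OR 2.028). If daily counts vary more than binomially, for example Poisson with mean 1.5, 22.3% of days are empty, the design effect is 1.15, and the 300-index ICC 0.1 figure is 2.05.

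**6. Slip refusal.** The article gives no rate. As an assumption only, 5%, 10% or 20% refusal on top of 270 leaves 256.5, 243 or 216 indexes, and the ICC 0 odds ratio is 2.06, 2.11 or 2.20.

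**The case against.** The strongest reply is that nothing is miscalculated: the table follows from its inputs, which are labelled as predictions for a trial that was not formally powered. That stands. The point concerns inputs, and no required sample size depends on them.

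Several stronger readings are tempting, and the article does not support them:

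- **That empty days raise the 1.96.** They do not. At ICC 0 only the number of indexes counts. An average of 1.5 over all 200 randomised days is also correct as an average. Empty days affect only the ICC 0.1 columns.
- **That 270 is the expected number.** It is an upper-case loss. An allowance is not a forecast, and a woman with one invalid assay may still be positive on another test. The article does not say whether the pilot's 30% is of women enrolled or of women with valid results. Proposed intervention also gives slips to women treated for a syndrome, which could offset part of the loss.
- **That refusal pushes the figure to 2.1 or 2.2.** The direction is plausible if slip holders are the denominator. However, Outcomes defines the primary measure over indexes, where refusal would not reduce the number analysed, and no refusal rate is given.
- **That 270 indexes go with 83 days per arm and a design effect of 1.12.** These mix two prevalence assumptions. The set that matches 270 is 79 days, mean size 1.70 and design effect 1.108.

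The size of the shift is also a fair objection. At ICC 0 the detectable rate moves by less than one percentage point, and moderate power remains a fair description at 76%. A completed trial would be read mainly from its confidence interval. This limits the importance of the point. It does not make the printed figures consistent with the section's own inputs.

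**Conclusion.** The concern holds in a limited form. The stated detectable effects are modestly too favourable. At 30% control and 80% power, the ICC 0 odds ratio lies between 1.96 and 2.03, the upper end requiring that the full 10% allowance is lost. The ICC 0.1 figure should be 2.03 rather than 1.99 even if all 300 indexes are reached, and about 2.10 with 270. The cluster result rests on 5 women per day and independent positivity at the stated prevalence. Any further loss from slip refusal cannot be sized from the article. Neither the design nor the planned analysis is put in doubt.

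**What to change.** Keep recruitment unchanged and restate the section as follows.

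1. Recompute the ICC 0.1 columns of Table 1 with the design effect for variable cluster size. The 30% row at 300 indexes becomes 2.03 (80% power) and 2.26 (90%).
2. Add rows for about 270 indexes. The 30% row is 2.03 / 2.26 at ICC 0 and about 2.10 / 2.35 at ICC 0.1. Say that this is the case in which the whole invalid-test allowance is used up.
3. Show lower numbers only as a labelled assumption about slip refusal.
4. Describe the 100 per arm as randomised clinic days, of which about 79 to 83 are expected to contribute an index.
5. Give the absolute difference beside the odds ratio at ICC 0: 30% to about 45.6% at 300 indexes, and to about 46.5% at 270.

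The cost is one recalculated table and a few sentences. The stated figures become slightly less favourable.

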### Statistical analysis

Simple point estimates for each arm will be presented by calculating the number of participants given a PN slip for whom at least one partner returned to the study clinic for treatment divided by the total number of participants given a PN slip. This was chosen over a mean of cluster responses, due to the higher importance of giving equal weight to each individual, over that of each cluster. Analysis will be by intention-to-treat. Analysis per protocol will also be conducted as a sensitivity analysis, based on the type of PN slip that was recorded as being given.

Trial arms will be compared using individual-level logistic regression, using robust standard errors to account for any clustering. Robust standard errors will be used, over generalised estimating equations or random effects models, as the expected correlation within clusters is minimal. Results will be presented as per the CONSORT extension for cluster trials
^
34
^.

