## Protocol

### Study design and setting

A cluster randomised trial will be embedded within the “IPSAZ study” (Investigating point-of-care diagnostics for sexually transmitted infections and antimicrobial resistance in antenatal care in Zimbabwe), a prospective interventional study being conducted in urban primary healthcare clinics (PHCs) in Harare province, Zimbabwe, aiming to evaluate a strategy for integration of point-of-care diagnostics for STIs into ANC settings
^
24
^. Such PHCs provide routine nurse-led antenatal care.

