### Randomisation and blinding

Randomisation of each clinic day will be performed in a 1:1 ratio between days where issued slips are associated with an incentive and days where no incentive is issued. Randomisation by clinic day was chosen as a method to allocate incentives, in preference to individual randomisation, to prevent contamination. Additionally, if some individuals presenting on the same day were offered an incentive and others were not, this may lead to a greater perception of unfairness amongst participants.

Randomisation will be performed by a statistician not involved in the IPSAZ study, using the formula “=INT(RAND()*2)” in Microsoft Excel for each clinic day. Randomisation outcomes will be recorded on a document produced for each month, and kept at each clinic site. The intervention team will refer to this document to determine whether it is an ‘incentive’ or ‘non-incentive’ day. For each individual pregnant woman, it will also be documented whether an issued PN slip was associated with an incentive or not. Similarly, when partners return it will be recorded if an incentive was provided. To ensure compliance with the randomisation log, this data will regularly be cross-checked to ensure that clients are being provided the correct slip based on day of attendance.

It is not possible to blind participants or researchers to the intervention. However, participants will only be informed of the availability of an incentive once they test positive on an incentive day and have already informed the clinical team how many PN slips are required. This is to prevent participants from providing an artificially elevated number of partners in order for incentives to be provided to individuals who are not actual partners of the index case. Of note, women could still return with a male who is not a sexual partner, and this would be difficult to detect. However, given the factors discussed regarding ensuring the health of the baby, and that this would still require disclosure of treatment to another male, we feel that the risk of this is low.

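### Clinic days are allocated by unrestricted coin flip across several clinics and no clinic term is named in the primary model: the test stays valid, but avoidable variance remains if partner return differs by clinic

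*Protocol article*

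**What the plan says.** All references are to the protocol article.

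- **Study design and setting:** the host project is "a prospective interventional study being conducted in urban primary healthcare clinics (PHCs) in Harare province, Zimbabwe". Clinics are plural; their number is not given.
- **Randomisation and blinding:** "Randomisation of each clinic day will be performed in a 1:1 ratio", and the draw is made "using the formula “=INT(RAND()*2)” in Microsoft Excel for each clinic day". No block, stratum or other restriction is described. "Randomisation outcomes will be recorded on a document produced for each month, and kept at each clinic site".
- **Statistical analysis:** "Trial arms will be compared using individual-level logistic regression, using robust standard errors to account for any clustering". No covariate is named and none is excluded. Arm summaries are simple proportions that weight each woman equally.
- **Sample size calculations:** the trial was not sized for this question. The zero ICC is argued from day of attendance alone; women seen on the same clinic day also share a clinic, and this is not mentioned.

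**The concern.** An independent draw for each day gives 1:1 only in expectation, both overall and within each clinic. With 100 days in a clinic, the 95% range is 40 to 60 incentive days. If clinics differ in how often partners come back, that chance imbalance moves the crude comparison. Robust standard errors count this variation in the interval but do not remove it; a clinic term or balanced allocation would.

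A difference between clinics is plausible. The rationale says that the incentive is meant to ease transport costs, and the amount was chosen to cover a return journey from most, not all, of the likely locations. The discussion adds that partners may go to whichever clinic is most convenient, where their visit would not count. At stake is precision in a trial that describes itself as only moderately powered.

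**Working it through.** **1. The plan's own figure.** Inputs from Sample size calculations: "an alpha of 0.05, a power of 0.8, an ICC of zero, 100 clusters per arm, and 1.5 participants per cluster", with 30% in the control arm, so 150 women per arm.

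- Intervention rate at OR 1.96: 0.30 × 1.96 / (0.70 + 0.30 × 1.96) = 0.588 / 1.288 = 0.4565.
- Pooled two-proportion test, two-sided 0.05: z = [0.1565 × √150 − 1.96 × √(2 × 0.3783 × 0.6217)] / √(0.2100 + 0.2481) = (1.917 − 1.344) / 0.677 = 0.846, so power is 80.1%.
- With design effect 1 + 0.5 × 0.10 = 1.05, the detectable odds ratio is 1.990.

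Both stated values (1.96 and 1.99) reproduce. This calculation contains no clinic component.

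**2. Variance of the risk difference.** Assumptions: 200 clinic days, each allocated separately at its site; equal numbers of days per clinic; women with a slip per day Binomial(5, 0.3); control rates averaging 30%; within-clinic OR 1.96. The spread between clinics is assumed, because the article gives none.

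Let W be the mean over clinics of p(1−p), summed over the two arms, and B the between-clinic variance of p, summed over the two arms. All women on one day belong to one clinic, so B is multiplied by E[m²]/E[m] = (1.05 + 1.5²)/1.5 = 2.2, where m is the number of women per day. In large samples:

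crude variance / clinic-standardised variance = 1 + 2.2 × B / W

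Example, two clinics at 15/45%. The intervention rates are 0.294/1.144 = 0.257 and 0.882/1.432 = 0.616.
- B = 0.0225 + 0.0322 = 0.0547.
- W = 0.1875 + 0.2138 = 0.4013.
- Ratio = 1 + 2.2 × 0.0547/0.4013 = 1.30.

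| Control rates by clinic | B | W | Formula | Simulated excess |
|---|---|---|---|---|
| 30/30% | 0 | 0.458 | 0% | about 0% |
| 25/35% | 0.0060 | 0.452 | 3% | about 2% |
| 20/40% | 0.0241 | 0.433 | 12% | about 10% |
| 15/25/35/45% | 0.0304 | 0.427 | 16% | about 13% |
| 15/45% | 0.0547 | 0.401 | 30% | about 29% |

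The simulated values sit slightly lower because standardising over clinics has a small cost of its own. The mean risk difference is the same under both analyses, so on this scale the gain is true precision.

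**3. Power on the odds ratio.** Simulated under the same assumptions with coin-flip days, 4,000 runs per setting, standard errors clustered on clinic day.

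| Control rates | No clinic term | Clinic term | Gain (points) |
|---|---|---|---|
| 30/30% | 80.5% | 80.3% | −0.2 |
| 25/35% | 78.6% | 79.4% | 0.8 |
| 20/27/33/40% | 75.9% | 77.6% | 1.7 |
| 15/25/35/45% | 71.3% | 76.4% | 5.1 |
| 20/40% | 72.2% | 77.4% | 5.2 |
| 15/45% | 62.4% | 73.2% | 10.8 |

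**4. Where that gain comes from.** At 20/40% the SD of the log odds ratio is 0.254 without and 0.256 with the clinic term, while its mean rises from 0.646 to 0.683. The adjusted model estimates a within-clinic odds ratio; the unadjusted one estimates a smaller marginal odds ratio. At 15/45% the marginal value is (0.4365/0.5635)/(0.30/0.70) = 1.81 when the within-clinic value is 1.96.

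**5. Type I error.** With coin-flip days, at 20/40%, 15/45%, 15/25/35/45% and 20/27/33/40%, the unadjusted test rejects 4.8, 5.3, 5.0 and 4.8% of the time. With the clinic term it rejects 5.4, 6.0, 5.7 and 5.3% (simulation error √(0.05 × 0.95/4000) = 0.34 points). With days balanced within clinic, the clinic-adjusted test gives 4.6, 4.9, 5.2 and 5.2%.

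**The case against.** The case on the other side is substantial.

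- **Silence is not exclusion.** The analysis section does not say the model is unadjusted, and a covariate list may sit in an analysis plan that is not shown. This stands as far as the model is concerned. It does not reach the allocation method, which the article itself fixes as an unrestricted draw.
- **Nothing is invalid.** A reader might infer that unrestricted allocation biases the comparison or inflates type I error. The documents do not support that: the unadjusted test holds its level at every spread tried. Chance imbalance could move the crude difference by about 5.0 points (two clinics at 15/45%) or 3.8 points (four clinics at 15 to 45%) in 95% of allocations. That movement is already inside the robust interval, whose half-widths with no effect are about 11.0 and 10.7 points.
- **Clinic is not a known prognostic factor here.** No return rate by clinic is reported, all sites are urban clinics in one province, and the discussion raises distance as an urban-rural matter. This stands: the spreads are assumptions, and moderate ones give little gain.
- **The power gain is not all noise removed.** This also stands. Nor do the lower unadjusted powers show that the protocol's 80% fails, because they are computed at marginal odds ratios below 1.96.
- **Days may already be balanced.** The text does not exclude one draw per calendar date shared by all clinics, which would largely balance them. References to each clinic day and to a log at each site suggest separate draws but do not settle it.

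**Conclusion.** The point holds as a cheap gain in efficiency, not as an error that threatens the result. Allocation is unrestricted across several clinics and the stated comparison names no clinic term. If return differs by clinic, the crude risk difference has avoidable variance: about 2% at 25/35%, 10% at 20/40%, 13% at 15/25/35/45% and 29% at 15/45%, and essentially none if clinics are alike. Power on the odds ratio rises by about 1 to 11 points across the unequal spreads, partly through the move to a conditional odds ratio, so the risk-difference figures are the fairer measure of what is lost.

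All of this rests on assumed clinic numbers and rates, equal clinic sizes and separate allocation at each site. The widest spread, 15/45%, implies a day-level ICC of 0.15²/0.21 = 0.107, close to the protocol's own 0.10 scenario; 25/35% implies 0.05²/0.21 = 0.012.

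**What to change.** In Statistical analysis, prespecify clinic as a fixed effect in the primary logistic model and state that standard errors are clustered on clinic day. Report the marginal, clinic-standardised risk difference from that model beside the odds ratio, say that the odds ratio is conditional on clinic, and keep the unadjusted result as secondary. Naming the primary analysis now also prevents a choice between crude and adjusted results once data are seen.

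For any days not yet randomised, balance incentive and non-incentive days within each clinic. The monthly list is already held at each site, so balancing adds no predictability that staff do not already have. The article does not say whether any days remain.

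The cost is a sentence or two; clinic is known for every woman. The downsides are the change from a marginal to a conditional odds ratio, which the marginal risk difference covers, and negligible benefit if the clinics prove similar.

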### Process evaluation

An accompanying mixed methods process evaluation will be conducted to further understand the PN process and the influence of incentives on uptake, within the broader IPSAZ study process evaluation, described in the main study protocol
^
24
^. This process evaluation follows the MRC process evaluation framework, with research domains including fidelity, coverage, responses to and interactions with the intervention, interactions and consequences, and context. Key aspects relevant for PN and this trial are feasibility, acceptability to both pregnant women and partners, how incentives influence interactions between the index case and their partners, and unanticipated pathways or consequences. Of note, assessments of acceptability will explore comparisons between standard PN, incentivised PN, and also no PN, which may be the most acceptable option for some participants. Methods include; in-depth interviews and focus group discussions with pregnant women, healthcare workers, members of the intervention team, and male partners; unstructured observations; and routine monitoring data. Unstructured observations will be of clinical encounters and will be conducted by a research assistant not involved with delivery of the intervention. As observation may impact consultations, permission will be requested from participants, confidentiality will be re-assured, and the research assistant will aim to be as unobtrusive as possible. Interviews with pregnant women and partners will be conducted after PN has been attempted or completed, in order to assess for unintentional consequences or adverse outcomes. As previously mentioned, negative consequences of PN will be documented during a post-natal telephone call.

